### **2.3.2 Known Potential Benefits**

#### **i) Participation in study may improve outcome in DV infections.**

The morbidity and mortality from DHF is often from a delay in seeking medical care. Parents in the study will be educated and encouraged to bring their infants to medical attention for febrile illnesses. Early medical evaluation of dengue can offset the severe consequences of the disease.

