**Data to be collected on infants hospitalized with acute febrile illnesses**

|                 |                                                                                                      |
|-----------------|------------------------------------------------------------------------------------------------------|
| Form data       | Date, Study ID no, subject initials, location code                                                   |
| Demographics    | Date of birth, gender                                                                                |
| Illness type    | Fever onset, symptoms, signs                                                                         |
| Hospital course | Clinical, laboratory, and radiographic data abstracted from medical record at end of hospitalization |

- ii) Non-hospitalized dengue- Each year during the peak DV transmission season from June to October, we will also conduct surveillance for DV infections that do not result in hospitalizations. During this time period, parents will be encouraged to bring their infants to the barangay health stations, local doctor's offices, or the City Health office if they develop an acute febrile illness. We will rely primarily on parents bringing their infants to the City Health office for febrile illnesses during the peak dengue season. In addition, nearly all pediatric health care providers in San Pablo will be aware of the study through education and information distributed through the local medical society and hospitals. Parents will be

reminded to present their study identification cards if they bring their infant with a fever > 38.0°C to a barangay health station or a private doctor's office. The health care personnel will be instructed to call a central telephone number where study personnel will coordinate transportation to the City Health office. There, study personnel will assess the infants, complete a questionnaire, and obtain an acute illness blood specimen (serum) for dengue diagnostic testing in addition to any routine clinical tests that may be requested by the treating nurse or physician. If the acute illness serum sample returns positive by DV IgM or RT-PCR, study personnel will arrange for collection of a convalescent blood specimen (serum) 10-14 days later.

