**Neutralizing Ab assays-** All subjects in the clinical study with evidence of DV infection (Categories I-IV) will have neutralizing anti-DV Ab titers determined in their pre-infection blood draw. The neutralizing Ab titers will be determined using a standard plaque reduction assay to reference DV isolates serotypes 1-4 [13]. We have previously shown that neutralizing Ab titers to reference DV isolates correlate well with neutralizing Ab titers to the actual infecting virus isolate [13]. The 50% plaque reduction neutralization titer will be calculated using 4-parameter curve fitting analysis.

**Peak viremia determinations-** We have found that viremia levels obtained within 72 hours of symptom onset in dengue are a good approximation of peak viremia levels [20-22]. A serotype specific, fluorogenic, quantitative RT-PCR assay will be performed on the acute illness serum samples collected within 72 hours of symptom onset from infants in Categories I-III.

**Ab-dependent enhancement of infection assay (ADE)-** All subjects in the clinical study with evidence of DV infection or likely exposure (Categories I-IV) will have an ADE Ab assay performed using their pre-infection blood draw.

**PBMC activation-** We recognize that limited numbers of PBMC will be available for study from the infant blood draws. Therefore, we plan to use modern multiplex assay techniques to get an overview of DV-induced immune activation patterns in infant PBMC. We will first perform the assays on serial collected PBMC (study visits 1 and 2) from 30 subjects without evidence of DV infection (Category V). This will allow us to refine the assays. Once optimized, the assays will be done on the pre-infection PBMC from all subjects with evidence of DV infection (Categories I-IV).

PBMC will be stimulated in vitro with DV and controls. At the early and late time points, cell culture supernatants will be collected and cellular RNA will be isolated. Pro- and anti-inflammatory cytokine/chemokine levels will be determined in the supernatants using a multiplex bead assay. 9 cytokines/chemokines will be assayed in a single sample using the preconfigured panel shown below:

| Category                    | Mediators                                                      |
|-----------------------------|----------------------------------------------------------------|
| Pro-inflammatory mediators  | IL-1 $\beta$ , IL-6, TNF- $\alpha$ , IFN- $\gamma$ , IL-12 p70 |

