## 7 STATISTICAL CONSIDERATIONS

### 7.1 Study Outcome Measures

- In order to achieve the first and second objectives of the study (Section 3), the primary outcome measure will be identification of DV infections and classification of dengue disease severity (described in Section 4, subpart IV). The primary outcome measure is categorical. Subjects with hospitalized DHF (Category I) will be rated as severity=5, and each step downward in severity category will be rated by a decrease in one point on a severity scale (4, 3, etc.).
- The secondary outcome measure, peak viremia level with DV infection, is also linked to the first and second objectives. It is a continuous variable associated with disease severity, the primary outcome measure.

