### 7.4 Analysis Plan

I. ***First study objective- correlate pre-existing, maternally-derived, neutralizing Ab titers against the infecting DV serotype with disease severity.***

Subjects with hospitalized DHF will be rated as severity=5, and each step downward in severity category will be rated by a decrease in one point on a severity scale (4, 3, etc.). Neutralizing Ab titers determined in the pre-infection blood draws, and predicted neutralizing Ab titers at the time of illness based on a kinetic model of anti-DV Ab clearance (see below), will be used for analysis. The association between pre-existing neutralizing Ab titers (raw and log-transformed) and severity of DV infections will be evaluated by fitting partial proportional odds multivariate longitudinal models [28, 29]. When needed, we will also use generalized estimating equations [30, 31], clustering on patient observations over time, while using a logit link function and unstructured error correlation structure. Analyses will be performed separately

for each DV serotype, as well as with all serotypes pooled (and serotype included as a candidate term in the model).

We will also compare pre-existing, maternally-derived, neutralizing Ab titers against the infecting DV serotype to peak viremia levels measured in subjects with symptomatic dengue. In this subset, we will fit a multiple linear regression model for peak viremia with neutralizing Ab titer levels, and other potential covariates. Model selection will be by partial F-tests [32] on the difference in residual error.

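### Viremia is assayed only in samples drawn within 72 hours of onset, so confirmed cases sampled later lack the secondary outcome, and time since onset is left to F-test selection

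*Protocol*

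**What the plan says.** **Assay rule.** Protocol Section 4, IV and Section 6.2.1 both set the same restriction: a "quantitative RT-PCR assay will be performed on the acute illness serum samples collected within 72 hours of symptom onset from infants in Categories I-III". The stated reason is that "viremia levels obtained within 72 hours of symptom onset in dengue are a good approximation of peak viremia levels", with earlier studies cited.

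**Case definition.** The clinical category table in Section 4, IV confirms Categories I-III by a positive RT-PCR or a positive IgM on the acute sample. It sets no limit on time from onset.

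**Role.** Section 7.1: "The secondary outcome measure, peak viremia level with DV infection, is also linked to the first and second objectives".

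**Analysis.** Section 7.4, I relates titre to viremia among symptomatic cases: "In this subset, we will fit a multiple linear regression model for peak viremia with neutralizing Ab titer levels, and other potential covariates". It then adds: "Model selection will be by partial F-tests". No covariate is named or held in the model, and nothing is said about symptomatic infants who have no 72-hour sample.

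**Timing data.** The form for hospitalised infants in Section 4, III records "Fever onset, symptoms, signs". Section 2.3.2 remarks that "The morbidity and mortality from DHF is often from a delay in seeking medical care", and says that parents will be encouraged to bring febrile infants in.

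**The concern.** The case definition and the assay rule use different time limits. An infant first sampled on day 4 can be a confirmed DHF case for the primary outcome and still have no secondary outcome, by rule. Section 7.4 describes the viremia analysis as covering symptomatic dengue, so a reader would not learn how many confirmed cases are absent or from which severity category.

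Among infants who do have a value, one draw anywhere in a three-day window stands for the peak. If levels change within that window, onset-to-draw time explains part of the variation. The plan allows for it only as an optional covariate. A significance test in a few dozen infants can easily discard a covariate that matters.

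At stake are the precision and possibly the validity of the titre-viremia slope, and how well DHF is represented in it.

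**Working it through.** **1. Infants available.** Section 7.2 expects 11 hospitalised DHF, 11 hospitalised DF and 44 non-hospitalised DF over four years: 11 + 11 + 44 = 66. The hospitalised count agrees with the plan's own rate: 22 / (4,000 × 4) = 0.1375% per year, inside the stated 0.1-0.2% (16 to 32 cases). No rate is given for the 44, so that count is taken as stated. No SD, effect size or power is given for viremia.

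**2. Infants left by the 72-hour rule.** Let h and o be the shares of hospitalised and outpatient cases sampled late. The documents give neither, so both are assumptions. Retained total = 22(1 − h) + 44(1 − o); retained DHF = 11(1 − h). The last column is the correlation detectable with 80% power at two-sided 5%, r = tanh[(1.960 + 0.842)/√(n − 3)], with n rounded.

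| h | o | Retained total | Retained DHF | Detectable r |
|---|---|---|---|---|
| 0% | 0% | 66 | 11 | 0.34 |
| 20% | 10% | 17.6 + 39.6 = 57.2 | 8.8 | 0.36 |
| 40% | 10% | 13.2 + 39.6 = 52.8 | 6.6 | 0.38 |
| 60% | 10% | 8.8 + 39.6 = 48.4 | 4.4 | 0.39 |
| 80% | 10% | 4.4 + 39.6 = 44.0 | 2.2 | 0.41 |

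A different assumption, normally distributed sampling day with mean 4 in hospital and 2.5 in outpatients (SD 1), gives Φ(−1) = 16% and Φ(0.5) = 69% within 72 hours. That is about 3.5 of 22 hospitalised (1.7 of 11 DHF) and 30.4 of 44 outpatients.

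**3. Effect of omitting time.** Suppose viremia falls by s log10 per day within the window, and sampling is δ days later per log10 of titre.
- Bias of the titre slope = −s × δ. It is zero if s = 0 (levels flat) or if δ = 0 (timing unrelated to titre). Neither quantity is in the documents.
- Residual variance without the time term = σ² + s²Var(t). With an assumed s = 0.8, residual SD in the 72-hour subset was 1.13 log10 without the term and 1.01 with it. The reduction is 1 − 1.01/1.13 = 10.6%, so the standard error of the titre slope is about 11% smaller even when there is no bias.

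**4. Would the F-test keep time?** This was simulated with 22 hospitalised and 44 outpatient cases, cut at 3 days. Assumptions: residual SD 1 log10, sampling-day SD 1, a true hospital-outpatient difference of 0.5 log10, and mean sampling day 3 versus 1.5 or 4 versus 2.5.

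| Assumed decline per day | 5% F-test drops time |
|---|---|
| 0.25 log10 | 74-84% of runs |
| 0.5 log10 | 25-56% of runs |

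Selection therefore often removes a term with a real effect at these sample sizes.

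**The case against.** **Levels within 72 hours approximate the peak.** The protocol says this and cites its sources, which are not at hand to dispute. A reader might infer a steadily falling curve inside the window. The documents do not show one, and if levels are flat there is no timing bias. This stands. It argues for a modest claim rather than for leaving time optional, because a fixed term costs one degree of freedom even if it proves unnecessary.

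**DHF infants selectively drop out.** This too is tempting, but it is inference. Section 2.3.2 links delay to DHF morbidity and mortality and gives no onset-to-sample times. The same paragraph plans education towards early presentation. In June to October an infant could also be sampled as an outpatient and admitted later. Later sampling of DHF cases is plausible, not established. Nor would a mainly outpatient viremia set prove selection, since 44 of 66 (67%) are expected to be outpatients with no loss at all.

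**The severity contrast is distorted.** In a simulation with mean sampling day 3.0 versus 1.5, a true hospital-outpatient gap of 0.5 log10 appeared as 0.35, 0.19 and −0.10 for declines of 0.25, 0.5 and 1.0 log10 per day. Section 7.4 plans no such contrast, however. It plans a slope of viremia on titre, and omitting time biases that slope only if timing is related to titre. A reader might also extend the problem to the DHF model, since Section 3 mentions viral load as a covariate. Section 7.4, II instead draws its covariates from the Section 7.1 table, which does not list viremia.

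**This belongs in an analysis plan.** Covariate lists and missing-data rules commonly do, and the wording leaves room for time since onset. But the protocol itself fixes F-test selection and the assay restriction, and no later analysis plan can use assays that were never run.

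**Late samples do not repair the analysis.** This is partly right. They measure viremia at presentation, and cases diagnosed by IgM alone have no RT-PCR serotype, so they cannot enter a model that needs titre against the infecting serotype.

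**Conclusion.** The point holds in a limited form. By rule, confirmed Category I-III cases sampled after 72 hours have no secondary outcome, and the analysis section does not acknowledge it. Time since onset may be dropped by F-test from a model with at most 66 infants.

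The documents do not allow the size or direction of any bias to be derived. Timing bias is zero if levels are flat within 72 hours or if timing is unrelated to titre. Under the assumed late shares the set shrinks from 66 to between 57 and 44 infants, with 8.8 to 2.2 DHF cases, and the detectable correlation rises from 0.34 to between 0.36 and 0.41. All of these figures rest on assumed presentation times.

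Only the secondary outcome is affected; severity classification needs no 72-hour sample. The change is still worth making because it is cheap and leaves the planned analysis intact.

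**What to change.** 1. **Section 7.4, I:** keep hours from fever onset to draw as a fixed covariate in the viremia regression, outside the F-test selection. Onset-to-draw time is already needed to apply the 72-hour rule; if only dates are held, use days.
2. **Section 7.4, I:** retain the within-72-hour set as the peak viremia analysis, and report by clinical category how many confirmed cases lack a 72-hour sample.
3. **Section 6.2.1:** as a supplementary analysis, run the quantitative RT-PCR on stored acute serum from later-sampled, RT-PCR-positive Category I-III cases. Label the result viremia at presentation and adjust it for time since onset. State that IgM-only cases without an RT-PCR serotype cannot enter the serotype-specific titre model.

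**Cost.** One degree of freedom and a few tens of extra assays at most: 66 − 57 = 9 to 66 − 44 = 22 under the table's assumptions, fewer if some late cases are RT-PCR-negative. No extra blood is needed, since Section 6.2.1 sets aside 1.0 ml of acute serum for repeat and future testing, and the yearly destruction rule in Section 6.2.2.1 covers only infants without DV infection.

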## **6.2.2 Specimen Collection, Preparation, Handling and Shipping**

### **6.2.2.1 Instructions for Specimen Preparation, Handling, and Storage**

Bar code labels with log numbers will be prepared in advance for the scheduled blood draws and acute/convalescent illness blood draws. Upon enrollment, mother and infant will each be given a unique study identifier. When blood is drawn from a study subject, one bar code label is automatically entered or placed in the data record and a duplicate bar code label is placed on the specimen. The bar code log numbers will be scanned into the specimen receiving database, which contains the study identifiers. Aliquots of plasma samples will be stored in -70°C freezers, and PBMC will be stored in liquid nitrogen at -120°C. Blood specimens will be stored at RITM, or at UMMS following RITM permission. Given the large number of blood specimens over the 4-year study period, it will be impossible to store all samples over the duration of the study and analysis periods. Samples from subjects without DV infections, and not identified as potential matched controls, will be destroyed following appropriate biosafety precautions on a yearly basis.

### **6.2.2.2 Specimen Shipment**

Specimens for QA checks of dengue diagnostic assays (EIA, RT-PCR) will be sent from RITM to AFRIMS, Department of Virology on a bimonthly basis over the first 2 years of the study. Specimens for QA checks of HAI serology and neutralizing Ab assays will be sent from RITM to AFRIMS, Department of Virology on an annual basis. Specimens for ADE assay, and PBMC/T-cell assays will be sent from RITM to CIDVR, UMMS on a semi-annual basis. All specimens will be coded, anonymous, samples, and sent on dry ice. Shipment protocols will follow the appropriate International Association Transportation Authority packing and shipping regulations.

## 7 STATISTICAL CONSIDERATIONS

### 7.1 Study Outcome Measures

- In order to achieve the first and second objectives of the study (Section 3), the primary outcome measure will be identification of DV infections and classification of dengue disease severity (described in Section 4, subpart IV). The primary outcome measure is categorical. Subjects with hospitalized DHF (Category I) will be rated as severity=5, and each step downward in severity category will be rated by a decrease in one point on a severity scale (4, 3, etc.).
- The secondary outcome measure, peak viremia level with DV infection, is also linked to the first and second objectives. It is a continuous variable associated with disease severity, the primary outcome measure.

#### Study Variables

| Variable                                                         | Measurement                | Time obtained                                                          |
|------------------------------------------------------------------|----------------------------|------------------------------------------------------------------------|
| Neutralizing Ab titers                                           | Continuous and categorical | Study visits 1 and 2 (pre-illness)                                     |
| ADE Ab assay                                                     | Continuous and categorical | Study visits 1 and 2 (pre-illness)                                     |
| PBMC activation assays                                           | Continuous and categorical | Study visit 1 or 2 (use single time point before illness for analysis) |
| IFN- $\gamma$ enzyme-linked immunoSPOT assay                     | Continuous and categorical | Study visit 1 or 2 (use single time point before illness for analysis) |
| Epidemiological and clinical data collected on case report forms | Binary and categorical     | Study visits 1 and 2, and at time of illness                           |

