Dengue is an emerging arboviral disease caused by infection with one of the dengue viruses (DVs), a group of four antigenically related mosquito-borne flaviviruses. The DVs are widespread throughout the tropics and produce significant morbidity and mortality in at least 1/2 million persons/year [1]. The World Health Organization (WHO) has categorized dengue as a high priority emerging viral disease, as over 1 billion people in the world are at risk for DHF. Infection with any 1 of the 4 DV serotypes (DV-1, DV-2, DV-3, DV-4) can produce a spectrum of illness. The manifestations of a DV infection range from asymptomatic or mild febrile illness, to the more symptomatic dengue fever (DF), to the most severe and potentially life-threatening illness, DHF. The cardinal feature of DHF, as in other viral hemorrhagic fevers, is rapid and severe vascular dysregulation. The vascular dysfunction contributes to thrombocytopenia, a coagulopathy, and, most importantly, a transient increase in vascular permeability. The circulating blood volume is reduced, hemoconcentration occurs, and, in severe cases, hypovolemic shock develops [2, 3]. Fluid resuscitation and intensive care can be life saving, but specific treatments are not available and often access to appropriate care is limited. So far, the main preventive strategy in dengue endemic countries is mosquito control of the primary DV vector, *Aedes aegypti*. Despite some success in a few countries, widespread mosquito control efforts have been difficult to sustain. Development of a vaccine is seen as the only practical strategy for effective prevention and long-term control of dengue disease. The vaccines under development that are likely to be considered for use in dengue endemic countries are live-attenuated or chimeric viruses combined in a tetravalent formulation. Beyond the problems of interference in multivalent viral vaccines, there are additional and somewhat unique

immunological issues in dengue that will pose challenges to mass, public health, vaccination campaigns against dengue.

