#### IV. Outcomes

i) **Primary outcome- Identification of DV infection and classification of disease severity.**

Study subjects will be classified into the clinical categories shown in the table on the next page. Clinical categories I and II will be identified by surveillance for hospitalized dengue. Category III will be identified by surveillance for non-hospitalized dengue during the peak DV transmission season. Category IV will be identified by hemagglutination inhibition (HAI) seroconversion between study visits #2 and #3 in the 250 infants selected for blood sample collection at study visit #3.

ii) **Secondary outcome- estimation of peak viremia levels.**

We have previously found that viremia levels obtained within 72 hours of symptom onset in dengue are a good approximation of peak viremia levels [20-22]. A serotype specific, fluorogenic, quantitative RT-PCR assay will be performed on the acute illness serum samples collected within 72 hours of symptom onset from infants in Categories I-III.

| Clinical Category                                    | Diagnostic Criteria                                                                                                                              | Lab Diagnosis of DV infection                                                                              | Serotype of infection                  | Primary DV infection                                         |
|------------------------------------------------------|--------------------------------------------------------------------------------------------------------------------------------------------------|------------------------------------------------------------------------------------------------------------|----------------------------------------|--------------------------------------------------------------|
| I. Hospitalized DHF                                  | 1. Acute febrile illness* requiring hospitalization, and
2. Lab diagnosis of DV infection, and
3. Meets WHO criteria for DHF.              | 1. + DV RT-PCR from acute illness serum sample, or
2. + DV IgM from acute illness serum sample.         | Determined from RT-PCR                 | IgM/IgG EIA pattern in paired acute and convalescent samples |

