The kinetics of serotype-specific anti-DV neutralizing Abs will be characterized in Filipino infants from 6-14 weeks to 16 months. We will do this using a two stage approach [33]. Serial plasma samples from 30 study subjects who did not have evidence of a DV infection from birth to 16 months, and born to DV-immune mothers (neutralizing Ab titers to  $\geq 2$  DV serotypes), will be collected. In the first stage, the elimination half lives ( $t_{1/2\beta}$ ) of neutralizing Abs to DVs 1-4 will be estimated from the slopes of linear fits to the log Ab titer concentrations over time for each subject. In the second stage, the serotype-specific  $t_{1/2\beta}$ 's will be fitted in linear regression models which will include Ab levels to the other serotypes and other covariates, i.e. factors which might impact maternal Ab decline or otherwise predict Ab levels. The significance of covariates will be assessed using F tests [32]. Model adjusted (least squares or estimated population marginal means [34]) estimates of these parameters with their standard errors will be generated. We will estimate the pre-existing anti-DV neutralizing Ab titers at the time of illness in symptomatic dengue cases using the previously constructed model. Neutralizing Ab titers will be estimated at which 25%, 50% and 75% of the subjects developed a symptomatic DV infection.

**II. Second study objective- measure the strength of association of anti-DV Ab effects (neutralization or enhancement) with development of DHF, controlling for other potential covariates.**

The variables that will be examined as potential covariates were selected to represent different aspects of the infant host response to primary DV infection, and are summarized in the table in Section 7.1. Using the pre-infection samples, potential risk and protective factors will be evaluated in multiple logistic regression analyses. Infants who develop hospitalized DHF will be the disease group (i.e. event), and the other subjects whose disease severity decreases at least one category on the disease severity scale will serve as controls. Models will be constructed in a stepwise manner using likelihood ratio chi-squared statistics to evaluate improvement in fit [35].

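### The candidate covariates of the DHF model include case-report-form data from the illness itself; if these enter, the antibody association may be masked or not estimable

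*Protocol*

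**What the plan says.** Protocol section 7.4, part II, describes one multiple logistic model for the second objective. The event is hospitalized DHF, the controls are subjects at least one severity category lower, and terms are chosen stepwise by likelihood-ratio statistics. Its potential covariates "are summarized in the table in Section 7.1".

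That table has five rows. The two antibody rows (neutralization and enhancement) are marked as pre-illness. The two cell-assay rows are limited to a single time point before illness. The fifth row, epidemiological and clinical data from case report forms, has no such limit and is timed "Study visits 1 and 2, and at time of illness".

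Section 4, III lists the content of the form for hospitalized infants. It includes fever onset, symptoms and signs, and the hospital course: "Clinical, laboratory, and radiographic data abstracted from medical record at end of hospitalization". Section 4, IV defines Category I by, among other criteria, "Acute febrile illness* requiring hospitalization, and" and "Meets WHO criteria for DHF". Section 2.1 describes the features of DHF: "The vascular dysfunction contributes to thrombocytopenia, a coagulopathy, and, most importantly, a transient increase in vascular permeability".

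**The concern.** Categories I and II share the criteria of hospitalization and laboratory-confirmed infection, and differ only in whether the WHO criteria for DHF are met. Category III differs from II in the absence of hospitalization. Among infants with symptomatic dengue, then, the event is assigned from hospitalization together with the clinical and laboratory findings on the illness forms. Section 7.4 makes those same items eligible predictors.

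Stepwise selection on improvement in fit favours a variable that partly restates the outcome. Once such a variable is in, the antibody term is judged only on the variation that remains, and with 11 events little may remain. The hospital course also exists only for Categories I and II, 11 + 11 = 22 expected infants. A model that uses it must therefore drop the other infants or assign them values.

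At stake is the only model the protocol states for the second objective, which is to measure the antibody-DHF association while controlling for other factors. A null antibody result could come from the covariate list.

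**Working it through.** **Inputs from the protocol.** Section 7.2 expects 11 hospitalized DHF, 11 hospitalized DF, 44 non-hospitalized DF and 32 mild/asymptomatic infections. The sum is 11 + 11 + 44 + 32 = 98, which agrees with the stated figure of nearly 100. The controls used here are the infected infants below Category I: 11 + 44 + 32 = 87.

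**Assumptions, not in the protocol.** The antibody measure is normal with an odds ratio of 2 or 3 per SD for DHF against all milder infections. The likelihood-ratio test is at 0.05. The illness variable is binary and independent of antibody given the outcome. Except for hospitalization, the frequencies of illness findings are assumed.

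**Step 1: how much of the outcome hospitalization explains.** This needs only the planned counts.

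- Null deviance: −2[11 ln(11/98) + 87 ln(87/98)] = 68.8.
- All 11 DHF infants are hospitalized by definition, as are 11 of the 87 controls (12.6%). The other 87 − 11 = 76 controls are not, and none of them is an event.
- Deviance with hospitalization in the model: −2 × 22 × ln(0.5) = 30.5, with nothing contributed by the 76.
- Likelihood-ratio chi-squared: 68.8 − 30.5 = 38.3 on 1 degree of freedom.

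Hospitalization would enter at any usual level. Because no event occurs without it, its coefficient has no finite estimate, and the 76 non-hospitalized controls then carry no information on antibody. The antibody term rests on 11 v 11.

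**Step 2: what this does to the antibody term.** Logistic models were simulated on 11 v 87. The table gives the power of the likelihood-ratio test for antibody. Where two figures appear, they come from separate sets of simulations, and the spread is of the size of simulation error.

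| Illness variable already in the model | Odds ratio 2 per SD | Odds ratio 3 per SD |
|---|---|---|
| None | 58–60% | 92–93% |
| Present in 80% of cases, 20% of controls | 50–52% | 86–89% |
| Hospitalization (100% v 12.6%) | 37% | 72–74% |
| Present in 100% of cases, 5% of controls | 26–30% | 46–47% |
| Reproduces the definition (100% v 0%) | 0% | 0% |

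Hospitalization, the 100% v 5% finding and the full definition were each stronger than antibody, and so would enter first, in essentially every run. The weak 80% v 20% finding was stronger in 90% of runs at an odds ratio of 2 and in 68% at 3.

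**The case against.** The best defence is that the authors meant something narrower. Section 7.4, part II, speaks of using pre-infection samples and of covariates chosen to reflect the infant host response. Section 3 frames the aim around pre-illness blood. The table is headed as study variables in general, its last row also holds harmless items such as gender, and a list of potential covariates is not a fitted model.

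Part of this stands. The items are candidates only, and nothing says that platelet counts or radiographs will be in the final model. But the references to samples govern blood assays, and case-report-form data are not samples. Four rows carry a before-illness limit, while the fifth extends to the illness. The protocol therefore states the list and states it wrongly for this model, so this is more than detail left to an analysis plan.

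A reader might infer that the model is bound to predict DHF from itself and that the antibody effect is certain to be lost. The documents do not support that: loss is total only if the selected items separate DHF completely, and a weak finding costs little. A reader might also infer that Category IV infants have no illness information at all. That goes too far, since the visit 3 form asks about hospitalization and febrile illness; what they lack is a dated dengue illness and its hospital course. Nor does the protocol state complete-case deletion, so a fall to 22 infants for missing data is one possible result and not the stated plan.

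The control set is itself not fully settled. Section 7.2 anticipates 200 or 300 matched uninfected controls, while section 6.2.1 limits the neutralization assay to Categories I–IV. The 87 used here follow the latter.

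**Conclusion.** The point holds as a defect in the stated covariate list. Section 7.4, part II, read with the section 7.1 table, makes outcome-defining and structurally incomplete illness-time data eligible for the DHF model, and no sentence excludes them. If they enter, the antibody association may be masked or not estimable.

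The result for hospitalization in Step 1 rests on the planned counts alone. The power figures also rest on the assumed odds ratios, the 0.05 level, the conditional independence of antibody and the illness variable, and a common antibody distribution in all controls. They show direction and rough size and do not forecast the trial's result. The defect concerns the model for the second objective; the severity model for the first objective is not affected by it.

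**What to change.** In section 7.4, part II, limit case-report-form candidates for the DHF model to data obtained before illness at visits 1 and 2, counting visit 2 only where it precedes the illness. Keep infecting serotype as a candidate term, as the section already provides. In the section 7.1 table, split the last row by time: visits 1 and 2 supply candidates, and time of illness supplies outcome classification only. Repeat in 7.4 that illness-time symptoms, signs, hospitalization and hospital laboratory and radiographic data serve only to classify the outcome.

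If age is wanted, use one defined for every infant, such as age at the pre-infection sample. Age at illness will not serve across Categories I–IV, because the 32 expected Category IV infants have no dated illness.

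Section 3 names viral load as a covariate, and section 4 measures it in acute-illness serum. That is a separate question. The edit should say that it leaves this covariate unchanged, so that sections 3, 7.1 and 7.4 stay consistent.

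The cost is a few sentences and one table row. No new data, samples or assays are needed.
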